### Participants

Eligible participants are those aged 10 to 12 years old and not yet in secondary school; located in Australia; who own or have access to a smartphone; have access to the Internet, an active email address and mobile phone number; who have age-appropriate English proficiency; and who can obtain their parent’s consent. Eligible participants are also required to be experiencing sleep disturbance, as determined by a total score of ≥ 2 (i.e., indicating 2–3 nights per week) on any of the first 5 items of the Paediatric Insomnia Severity Index (PISI) reported by the parent at screening. Ineligible participants are those who currently meet or have previously met the criteria for a MDD diagnosis as determined by parent report on the mood module of the Kiddie Schedule for Affective Disorders and Schizophrenia (KSADS-COMP) [26] at baseline.

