**ASSESSMENTS**:						
*Primary Outcome*						
**Sleep problems** Paediatric Insomnia Severity Index - Adolescent (PISI-A); Child self-report		X		X	X	X
*Secondary Outcomes*						
**Sleep problems** Paediatric Insomnia Severity Index (PISI); Parent self-report		X		X	X	X
**Depressive symptoms** The Revised Child Anxiety and Depression Scale – 25; Subscale (RCADS-25); Parent self-report		X		X	X	X
The Revised Child Anxiety and Depression Scale – 25; Depression Subscale (RCADS-25); Child self-report		X		X	X	X
**Anxiety Symptoms** The Revised Child Anxiety and Depression Scale − 25; Anxiety Subscale (RCADS-25); Parent self-report		X		X	X	X
The Revised Child Anxiety and Depression Scale – 25; Anxiety Subscale (RCADS-25); Child self-report		X		X	X	X
**Daytime Sleepiness** The Epworth Sleepiness Scale; Child self-report		X		X	X	X
**Sleep Quality** Sleep Quality Question; Child self-report		X		X	X	X
**Dysfunctional beliefs about sleep** The Dysfunctional Beliefs and Attitudes about sleep (DBAS); Child self-report		X		X	X	X
**Pre-sleep hyperarousal and anxiety** The Sleep Anticipatory Anxiety Scale (SAAQ) Adolescent Version; Child self-report		X		X	X	X
**Repetitive Negative Thinking** The Persistent and Intrusive Negative Thoughts Scale (PINTS); Child self-report		X		X	X	X
**Quality of Life** The Child Health Utility 9D (CHU-9D); Child self-report		X		X		
**MDD Diagnosis** Kiddie Schedule for Affective Disorders and Schizophrenia (K-SADS-COMP; assessment of Mood disorders only); Parent self-report		X				X
*Additional study measures*						
**Registration details** Registration Questionnaire; Parent self-report		X				
**Demographics** Demographics Questionnaire; Parent self-report		X				
**Recent mental health care** Mental Health Care Questionnaire; Parent self-report		X		X	X	X
**Previous use of mobile apps for sleep** Mobile app questionnaire; Parent self-report		X				
**Digital program satisfaction** Satisfaction Questionnaire; Child self-report				X		
**Treatment Adherence*** Treatment adherence; Parent self-report				X		
**Withdrawal reasons** Withdrawal question		X	X	X	X	X

*Note.* *Assessed in the intervention group only

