Each study assessment contains questionnaires in relation to the child participant, with the baseline and 9-month follow-up assessment also containing a diagnostic assessment. Some questionnaires are to be completed by the parent (parent-report) and other questionnaires are to be completed by the child (child-report). Participants will have 14 days to complete the baseline assessment and 7 days to complete all other study assessments and will be sent two reminders (Days 3 and 5). All study assessments can be completed using any Internet-enabled device and include both parent- and child-reported measures. The research team will be available for contact throughout the trial period to participants in case assistance is needed, with research team contact details being provided on the study webpage, the Participant Information Sheet, and at each assessment. However, contact with participants will not be proactive or therapeutic in nature. Participants will be reimbursed $10AUD (electronic gift voucher sent to parents via email) for each study assessment and diagnostic assessment ($60AUD total). Discontinuation of the allocated intervention will occur if the participant withdraws from the trial or if they are no longer able to engage in the intervention due to a change in circumstances (e.g., reside outside Australia).

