### Primary outcome

#### Insomnia symptoms (child-reported)

The primary outcome will be child reported insomnia, using the Paediatric Insomnia Severity Index – Adolescent (PISI-A). This measure is adapted from the original Paediatric Insomnia Severity Index, completed by parents. The measure contains 6-items. Items 1 to 5 assess the frequency of insomnia-related symptoms including difficulty falling asleep, nighttime wakings, and daytime sleepiness, which are all rated on a 6-point Likert scale from Never − 0 nights (0) to Always − 7 nights (5). Total sleep duration (item 6) is rated on a 6-point scale estimating total hours of sleep on most nights, where a lower score indicates more hours of sleep (0 = 11–13 h; 5 = less than 5 h). This measure has good validity and reliability in children aged 11–18 years [32–34]. The selection of a child-rated measure, over a parent-report measure was based on data showing parents of children aged 10–12 years are often unaware of their child’s sleep difficulties [11].

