### Secondary outcomes

#### Insomnia symptoms (parent-reported)

The Paediatric Insomnia Severity Index (PISI) is a parent-reported measure of insomnia severity, which assesses the International Classification of Sleep Disorders (ICSD-II) general criteria for insomnia (i.e., difficulties falling asleep, difficulties maintaining sleep, and daytime impairment). The measure contains 6-items. Items 1 to 5 are rated on a 6-point Likert scale from Never − 0 nights (0) to Always − 7 nights (5). Total sleep duration (item 6) is rated on a 6-point scale estimating total hours of sleep on most nights, where a lower score indicates more hours of sleep (0 = 11–13 h; 5 = less than 5 h). The total score will be used (range: 0–30). The PISI has adequate validity and reliability in children aged 4 to 10 years [32, 33, 35]. As the child-reported sleep measure (PISI-A) is validated for children aged 11 years and above, we chose to include a parent-reported measure of child insomnia to ensure a validated measure of insomnia is included for participants aged 10 years old.

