### Monitoring

The current trial will be overseen by a Trial Management Group to supervise the conduct and safety of the trial in accordance with the guidelines on Data Safety Monitoring set by the National Health and Medical Research Council [52]. Parents of participants who report an Adverse Event (AE), which includes severe insomnia symptoms (indicated by a score of 5 on item 6 of the PISI) reported at the tertiary endpoint (9-months post-baseline), will receive a pop-up message in the questionnaire with recommendations to seek support from a health professional for their child. A call-back from a psychologist on the research team will also be offered. Participants who report an AE that includes severe depressive symptoms (indicated by a total t-score ≥ 70 on the RCADS) reported at the tertiary endpoint (9-months post-baseline) will receive a pop-up message in the questionnaire recommending that they tell a trusted adult about how they are feeling and seek help from a health professional. They will be provided with information about where to seek help and informed that we will let their parents know they are having a hard time. An email will be sent to the parent or guardian’s email address informing them of their child’s response with the option of a call-back from the team Psychologist. To examine rates of symptom deterioration, an increase of seven points on the PISI-A will be used as the threshold to indicate reliable symptom deterioration at the primary endpoint. This criterion is based on a α = 0.8 and a SD = 5.4 as recommended by Jacobson and Truax [53] and Byars and Simon [32]. All adverse events and serious adverse events and broader safety monitoring will be documented and reported to the Trial Management Group and to the University of New South Wales Human Research Ethics Committee by the Clinical Trial Manager and reported in the primary outcomes paper. If there are concerns for participant safety, based on (but not limited to) a higher than anticipated rate at one or more of the endpoints, the Trial Management Group may recommend pausing or terminating the trial. The University of New South Wales may audit trial conduct and procedures at any time and this process will be independent of the investigators and the sponsor.

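### The only trigger named for the 9-month severe-insomnia alert is item 6 of the parent PISI; the matching child PISI-A item, collected at the same assessment, has no described response

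*Protocol article*

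**What the plan says.** All references are to the protocol article.

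- **Monitoring, insomnia.** The adverse event that prompts a response is "severe insomnia symptoms (indicated by a score of 5 on item 6 of the PISI) reported at the tertiary endpoint (9-months post-baseline"). Parents then see a pop-up advising professional help for the child, and a psychologist call-back is offered.
- **Monitoring, depression.** A severe RCADS score at 9 months produces a pop-up addressed to the child. In addition, "An email will be sent to the parent or guardian’s email address informing them of their child’s response", with a call-back option.
- **Monitoring, deterioration.** A rise of seven points on the PISI-A at 6 weeks marks reliable deterioration. It is used to examine rates, and no action for the individual child is attached.
- **Table 1.** The primary outcome is listed as "Paediatric Insomnia Severity Index - Adolescent (PISI-A); Child self-report". It and the parent PISI are both scheduled at baseline, 6 weeks, 3 months and 9 months.
- **Insomnia symptoms (child-reported).** Child report was preferred because "parents of children aged 10–12 years are often unaware of their child’s sleep difficulties".
- **Blinding.** Investigators, the trial manager and research assistants can use the Qualtrics data to contact participants who have adverse events.

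**The concern.** The alert exists to prompt help for a child who sleeps less than 5 hours on most nights. As described, it fires only if the parent reports this. A child who gives that answer when the parent does not is outside the named criterion, although the answer has already been recorded.

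This sits awkwardly with the article's own reasoning. The primary outcome is child-reported because parents may not know, but the insomnia alert relies on the parent alone. The same paragraph of Monitoring already has a route that starts from the child's answers, but only for depressive symptoms.

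At stake are two things: help reaching some children, and possibly the count of severe-insomnia events. Adverse events go to the Trial Management Group, the ethics committee and the primary outcomes paper. If the named criterion is also the counting rule, events reported only by the child would not be counted.

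**Working it through.** This is mainly a check of the text.

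**1. Which form is meant.** Insomnia symptoms (parent-reported) defines PISI as the parent measure. Insomnia symptoms (child-reported) gives the child measure its own name, PISI-A. Monitoring keeps the two apart: PISI for the alert, PISI-A for deterioration. The alert sentence is loose about who reports the event, but the instrument named and the pop-up to parents both point to the parent form.

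**2. Whether the items match.** Both sections describe item 6 as total sleep duration on a 6-point scale, 0 = 11–13 h and 5 = less than 5 h. The full item wording is not shown, so the match is one of described content and anchors.

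**3. Whether the child's answer is available.** Table 1 marks both forms at 9 months.

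**4. Whether anything else responds to it.** The PISI-A appears once in Monitoring, in the deterioration criterion. With the stated reliability of 0.8 and SD of 5.4, and the usual multiplier of 1.96:

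1.96 × 5.4 × √(2 × (1 − 0.8)) = 6.69, which rounds up to the stated 7 points.

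That figure is sound, but it is a change in total score at 6 weeks, not an item 6 score at 9 months. The staff access described under Blinding refers back to adverse events as set out in Monitoring and adds no child trigger.

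**5. Scale, by assumption only.** The document gives no rate of item 6 = 5 and no parent–child agreement figure. Suppose 0.5% to 5% of assessed children score 5 on the PISI-A but not on the PISI.

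- If 9-month attrition equals the 40% planned for 6 weeks: 214 × (1 − 0.40) = 128.4 assessed. Then 0.005 × 128 = 0.6 and 0.05 × 128 = 6.4 children.
- With no attrition: 0.005 × 214 = 1.1 and 0.05 × 214 = 10.7 children.

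**6. Age and validation.** The article says of the PISI-A: "This measure has good validity and reliability in children aged 11–18 years". At the 9-month assessment, only children enrolled in the first 3 months of age 10 are still 10.

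| Assumed entry ages | Still 10 at 9 months | Aged 11 or over |
|---|---|---|
| Uniform over 10–12 | 3/36 = 8.3% | 91.7% |
| Uniform over 10–11, none aged 12 | 3/24 = 12.5% | 87.5% |
| All enrolled at age 10, uniform within the year | 3/12 = 25% | 75% |

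The parent PISI is stated to be valid for ages 4 to 10. Under each assumption, most children at 9 months are therefore inside the stated range of the child form and above that of the parent form.

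**The case against.** **This is a condensed article.** Alert logic by informant is detail that a full protocol may hold, and the adverse-event definition is worded as inclusive, not exhaustive. That stands as a limit: a child trigger may exist elsewhere. But the article does not merely stay silent. It states an instrument, an item and a threshold, and that stated rule is the point at issue.

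**Other provisions catch these children.** A reader might infer that every other safeguard depends on the parent noticing or the family making contact, because the article says that "contact with participants will not be proactive or therapeutic in nature". The document does not support that. Blinding provides for staff to contact participants with adverse events, and the depression email starts from the child's answers without the family asking. A reader might also infer that child-reported insomnia plays no part in safety monitoring; the 6-week PISI-A criterion shows otherwise. Still, neither provision names a child item 6 score as a trigger, so the gap narrows without closing.

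**The parent trigger is sensible.** The advice is addressed to parents, and these parents are not typical. Eligibility required a qualifying score "on any of the first 5 items of the Paediatric Insomnia Severity Index (PISI) reported by the parent at screening", and they rate the PISI again at every follow-up. They are also asked at follow-up whether their child needed mental health support. This stands, and it is why the group missed may be small. It supports keeping the parent trigger, not having it as the only one.

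**The child form is not validated at every age.** The article itself says: "As the child-reported sleep measure (PISI-A) is validated for children aged 11 years and above". This stands for children still aged 10, a minority at 9 months under each assumption shown.

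**A single sleep-duration item need not be handled like mood risk.** Fair: the depression route is a convenient model, not a binding precedent.

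**Conclusion.** The point holds in a limited form. The only severe-insomnia trigger named for 9 months is the parent PISI item 6. The corresponding child item is collected at the same assessment and has no described response, despite the article's own doubt about parental awareness.

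The number of children affected cannot be estimated from the document. The range of roughly 1 to 11 children rests entirely on the assumed 0.5% to 5% discordance and shows scale only. Under-counting of adverse events is conditional on the alert criterion also being the counting rule, which the article does not settle. It would go too far to say that the trial disregards children's reports, or that its safety monitoring fails. The primary analysis and sample size are not touched. This is an inexpensive safety improvement that should be made, not a flaw in the trial's main inference.

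**What to change.** In Monitoring, trigger the alert and count the adverse event when item 6 equals 5 at 9 months on either the parent PISI or the child PISI-A. Keep the present parent response as it is. For an alert raised by the child's answer, use the route already described for depression: a pop-up to the child, an email to the parent and the offer of a call-back. Report the counts by informant and by arm. If the full protocol already has a child trigger, it is enough to say so.

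No new data are needed. The costs are Qualtrics display logic, a short amendment to participant-facing safety wording (which would probably need ethics approval), some extra psychologist call-back offers, and some false alarms from a single item, notably in children still aged 10. The child's answer would also be passed to the parent, as already happens for depression.

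### The 9-month insomnia and depression adverse events are symptom levels with no baseline reference, so the reported rate can mix unchanged pre-existing severity with new worsening

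*Protocol article*

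**What the plan says.** All references are to the protocol article.

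- **Adverse event, insomnia (Monitoring).** The event is "severe insomnia symptoms (indicated by a score of 5 on item 6 of the PISI) reported at the tertiary endpoint (9-months post-baseline"). Item 6 is sleep duration, "where a lower score indicates more hours of sleep (0 = 11–13 h; 5 = less than 5 h"), so the event is a parent report of less than 5 hours of sleep.
- **Adverse event, depression (Monitoring).** An RCADS total t-score of 70 or more at 9 months is handled in the same way, again as a level.
- **Change-based criterion (Monitoring).** Separately, "an increase of seven points on the PISI-A will be used as the threshold to indicate reliable symptom deterioration at the primary endpoint". It is derived from a reliability of 0.8 and an SD of 5.4.
- **Reporting (Monitoring).** All adverse events go to the Trial Management Group and the ethics committee, and into the primary outcomes paper. The group may recommend a pause or termination "based on (but not limited to) a higher than anticipated rate at one or more of the endpoints".
- **Entry (Participants).** "Eligible participants are also required to be experiencing sleep disturbance", defined as a score of at least 2 "on any of the first 5 items of the Paediatric Insomnia Severity Index (PISI) reported by the parent at screening". Current or past MDD by parent report excludes a child. No upper limit is set on item 6 or on the RCADS.
- **Schedule (Table 1).** "Paediatric Insomnia Severity Index (PISI); Parent self-report" is marked at baseline, 6 weeks, 3 months and 9 months. So are the parent and child RCADS-25.

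**The concern.** An adverse-event rate is read as what happened to participants after allocation. A level measured once, at 9 months, does not show that. A child whose parent reports under 5 hours of sleep at entry and again at 9 months has not worsened, yet is counted. A child who worsens a great deal but does not end in the extreme category of item 6 is not counted.

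What is at stake is whether the published harms rate can be interpreted. If some children start at these levels, the rate is partly persistence of severity present at entry and partly new worsening, and a reader cannot tell how much is which. Randomisation balances how many children start at the level, on average. It does not balance how many remain there, because persistence is something an effective sleep intervention would be expected to reduce.

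**Working it through.** **1. The plan's own change threshold reproduces.** The Jacobson-Truax reliable change is 1.96 × SD × √(1 − r) × √2. With SD = 5.4 and r = 0.8 the standard error of measurement is 5.4 × √0.2 = 2.415, the standard error of a difference is 2.415 × √2 = 3.415, and the threshold is 1.96 × 3.415 = 6.69. On an integer scale that is 7, as stated. The 9-month levels have no stated derivation or expected rate to reproduce.

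**2. What each criterion catches.** For the parent PISI, "The total score will be used (range: 0–30"): items 1 to 5 carry 25 points and item 6 carries 5.

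- Item 6 = 5 at baseline and at 9 months: an adverse event with no change.
- Item 6 from 0 to 4: no adverse event.
- Items 1 to 5 rising from the minimum entry score of 2 to 25, a worsening of 23 points: no adverse event unless item 6 is 5.
- The seven-point rule does not close these gaps. It is on the child form and at 6 weeks, and a move of 0 to 5 on item 6 alone adds 5 points, short of 7. No change-based criterion is stated for 3 or 9 months.

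**3. How large the overlap could be.** The documents give no baseline prevalence of item 6 = 5, no persistence and no onset rate, so what follows is assumption. Let p be the proportion at item 6 = 5 at baseline, q the proportion of those still there at 9 months, and o the proportion of the rest who newly reach it. With no treatment effect,

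pre-existing share = pq / (pq + (1 − p)o),

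which does not depend on sample size. Two sets of assumptions were used. Set A has p 1–10%, q 50–80%, o 1–3%. Set B has p 5–20%, q 30–70%, o 1–3%.

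| Set | p | q | o | pq | (1 − p)o | Share |
|---|---|---|---|---|---|---|
| A, lowest | 1% | 50% | 3% | 0.0050 | 0.0297 | 14% |
| A, highest | 10% | 80% | 1% | 0.0800 | 0.0090 | 90% |
| B, lowest | 5% | 30% | 3% | 0.0150 | 0.0285 | 34% |
| B, highest | 20% | 70% | 1% | 0.1400 | 0.0080 | 95% |

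Together the sets span about 14% to 95%. Other choices move the ends: p = 1%, q = 30%, o = 3% gives 0.0030 / 0.0327 = 9%.

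**4. In counts.** With 214 / 2 = 107 per arm, no dropout and set A, carried-over cases run from 107 × 0.01 × 0.5 = 0.5 to 107 × 0.10 × 0.8 = 8.6 per arm. New cases run from 107 × 0.90 × 0.01 = 1.0 to 107 × 0.99 × 0.03 = 3.2 per arm. The numbers are small either way, so a few persisting cases can dominate the rate.

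**The case against.** The strongest reply is that the levels serve mainly as a duty-of-care flag. They prompt a message and an offer of contact, and for that an absolute level is sensible whatever the child's history. This stands, and the fix does not touch it. It does not cover the second use of the same events, as a reported adverse-event rate.

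Three stronger readings are tempting, and the documents do not support them.

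- **That the plan counts the entry condition itself as harm.** Entry rests on the frequency items 1 to 5. The adverse event is the most extreme category of item 6, which plays no part in eligibility. Overlap is possible, but its size is unknown and could be small. For depression, the MDD exclusion probably reduces it further, although it does not exclude a high RCADS score.
- **That new harm is hidden.** The seven-point PISI-A criterion refers to baseline and reproduces, so worsening at 6 weeks is examined. The gap is at 3 and 9 months. One can construct a case in which benefit masks harm. With 64 per arm (214 × 0.6 / 2, carrying the 40% attrition to 6 weeks forward to 9 months) and p = 10%, take persistence of 20% on the app against 50% on control, and onset of 4% against 1%. Counted events are then 1.28 + 2.30 = 3.58 against 3.20 + 0.58 = 3.78. But this needs the app to more than halve persistence while quadrupling onset, with values outside the ranges assumed above. It shows a possibility, not an expectation.
- **That the pause provision is driven by this event and cannot respond to harm.** The provision names no event, is expressly not confined to a rate, and leaves judgement to the Trial Management Group. The absence of an anticipated rate is detail that an article may leave to the full protocol.

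**Conclusion.** The point holds as a matter of reporting. As written, the 9-month insomnia and depression adverse events are levels without a baseline condition, and nothing in the eligibility criteria removes children already at those levels. The reported rate can therefore combine unchanged severity with new worsening, and no change-based criterion at 3 or 9 months separates them.

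The size cannot be derived from the documents. The span of about 14% to 95% for the pre-existing share concerns item 6 only. It rests entirely on assumed prevalence, persistence and onset with no treatment effect. No corresponding figure is offered for the RCADS level. The primary efficacy analysis is not affected. This is a cheap improvement to the harms reporting, not a flaw in the trial's safety oversight.

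**What to change.** Leave the pop-up message, the call-back offer and the pause provision exactly as they are. In the adverse-event tabulation, use the baseline PISI and RCADS to show, by arm and for each level, children who newly meet it at 9 months separately from those who also met it at baseline. In the same section, reconcile the 9-month level-based flags with the 6-week change-based criterion, so that a reader knows which measure describes deterioration at which assessment.

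The cost is a sentence or two and one split in a table, using data already scheduled. The small downside is that the new-onset count contains fewer events, so that rate is less precise. Showing both rows keeps the total available.

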#### Depressive symptoms

Parent- and child-reported depressive symptoms will be measured by the depression subscale of the Revised Children’s Anxiety and Depression Scale-25 (RCADS-25) Parent Report and the RCADS-25 Child Report [36]. The depression subscale measures symptoms of depression in children and adolescents aged 8 to 18 years. Ten items assess the frequency of symptoms and are rated on a 4-point Likert scale from Never (0) to Always (3). The total score will range from 0 to 30, with higher scores indicating higher severity of depressive symptoms. Both the parent and child versions have good psychometric properties [37] and are consistent with current guidelines for the assessment of mental health in children [38].

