#### Anxiety symptoms

Parent- and child-reported anxiety symptoms will be measured by the anxiety subscale of the Revised Children’s Anxiety and Depression Scale-25 (RCADS-25) and the RCADS-25 Child Report [36]. Fifteen items assess anxiety symptoms as rated by the parent and child and a rated on a 4-point Likert scale from Never (0) to Always (3), with total scores ranging from 0 to 45. Higher scores indicate higher severity of anxiety symptoms. The Total Anxiety subscale has been found to have good to excellent internal consistency and good to excellent reliability in school and clinical samples [37, 39].

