### Data collection, management, and statistical methods

Participant data will be collected and securely stored on the University of New South Wales (UNSW) OneDrive which are hosted on servers provided by the UNSW at GovDC Data Centres in Sydney, Australia. The data is stored in a SQL Server 2016 database, which undergoes daily backups and is supported by 128-bit encryption. To ensure participant confidentiality, at the data analysis stage, each participant will be assigned and only identified by a unique identification code.

For analyses, all study data will be exported from the Qualtrics Survey Platform to SPSS Version 26 using a Microsoft Excel file format. Files with identifiable data will be stored on UNSW OneDrive and once deidentified by authorized members of the research team for analysis will be stored on a secure sever. Any personally identifiable information, such as participant names, email addresses, mobile phone numbers, IP addresses, free response data, will be removed from the outcomes analysis file. Only the research team listed on the project will have access to identifiable study assessment data, while aggregate deidentified data will be retained for future evidence synthesis.

Analyses will be conducted to determine the effect of the interventions on insomnia symptoms at the primary and secondary endpoints. Analyses will be undertaken on an intention-to-treat basis, including all participants randomised, regardless of the intervention received. The effectiveness of the trial intervention will be established using mixed-model repeated measures (MMRM) analyses due to the inclusion of participants with missing data with this approach. The primary hypothesis will be evaluated by a contrast evaluating change in child-reported insomnia symptoms between baseline and 6-weeks post-baseline (primary endpoint), based on the interaction between time and condition. The same approach will be used for secondary outcomes. Adherence and acceptability of the intervention will be described.

Exploratory analyses will compare proportion of young people who meet criteria for MDD at the tertiary endpoint, as well as those showing significant symptoms of depression, operationalised as a t-score of greater than 65 on the RCADS.

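### The adverse-event trigger for severe depressive symptoms uses an RCADS total t-score without naming the subscale; read literally, 60% of that score is anxiety items

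*Protocol article*

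**What the plan says.** The Depressive symptoms section of the protocol article assigns the construct to one subscale: "depressive symptoms will be measured by the depression subscale of the Revised Children’s Anxiety and Depression Scale-25". It describes that subscale as "Ten items assess the frequency of symptoms and are rated on a 4-point Likert scale", and adds "The total score will range from 0 to 30". The Anxiety symptoms section covers the rest of the instrument: "Fifteen items assess anxiety symptoms as rated by the parent and child", "with total scores ranging from 0 to 45".

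The Monitoring section then defines an adverse event, assessed at 9 months, as "severe depressive symptoms (indicated by a total t-score ≥ 70 on the RCADS". It names no subscale. A child who meets the criterion sees a pop-up advising them to tell a trusted adult and seek help. The parent is emailed and offered a call-back from the team psychologist. Adverse events go to the Trial Management Group and the ethics committee and are reported in the primary outcomes paper.

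The statistical methods section has an exploratory comparison of children with significant depressive symptoms, "operationalised as a t-score of greater than 65 on the RCADS". It names no subscale either, but does not use the word total.

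**The concern.** The event carries a depression label, but the score that triggers it is described as a total on an instrument that also measures anxiety. If the survey is built to the letter of the Monitoring section, the label and the score measure different things, and two errors become possible. A child with high depression and low anxiety may fall short of the cut-off on the total, and so miss the pop-up, the parent email and the call-back offer. A child whose symptoms are mainly anxiety may pass the cut-off and be counted as a severe-depression event.

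The first error affects a live alert to a child and parent, which a later analysis plan cannot restore. The second affects the event counts on which the Trial Management Group may recommend pausing or stopping the trial, and which the primary paper will report.

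**Working it through.** **Composition of the score (figures from the article).** Depression: 10 items × 3 = 30 points. Anxiety: 15 items × 3 = 45 points. Both products reproduce the stated ranges. Together they make 25 items and 75 points. The anxiety share is 15/25 = 45/75 = 60%.

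**How far the two scores could disagree (assumptions).** The documents give no subscale correlation, SD or norms, so the following is illustrative:

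- D and A, the depression and anxiety scores as deviations from their norm means, are bivariate normal with correlation r = 0.5 to 0.8.
- Per-item spread is equal, so with SD(D) = 1, SD(A) = k = 1.5.
- Total = D + A. Each t-score has norm mean 50 and SD 10, so t = 70 is z = 2.

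The SD of the total is s = √(1 + k² + 2rk), and its correlation with depression is ρ = (1 + rk)/s.

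- r = 0.5: s = √(1 + 2.25 + 1.5) = √4.75 = 2.179; ρ = 1.75/2.179 = 0.803.
- r = 0.8: s = √(1 + 2.25 + 2.4) = √5.65 = 2.377; ρ = 2.2/2.377 = 0.926.

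Missed share = 1 − P(both t ≥ 70) / P(depression t ≥ 70). The share of flagged children below 70 on depression has the same numerator term over P(total t ≥ 70). In the shifted case each subscale mean is 1 SD above norm, so the mean of the standardised total is (1 + k)/s.

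| r | ρ | Missed, norm level | Flagged but depression t < 70, norm level | Missed, +1 SD | Flagged but depression t < 70, +1 SD |
|---|---|---|---|---|---|
| 0.5 | 0.803 | 56% | 56% | 30% | 44% |
| 0.6 | 0.845 | 51% | 51% | 27% | 39% |
| 0.7 | 0.886 | 44% | 44% | 24% | 33% |
| 0.8 | 0.926 | 36% | 36% | 20% | 26% |

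The spread assumption matters somewhat. With equal subscale SDs (k = 1), the missed share is 30–47% at norm level and 16–23% under the shift.

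**Two example children (k = 1.5).**

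- Depression t = 70, anxiety t = 50: total t = 50 + 10 × 2/s = 59.2 (r = 0.5) or 58.4 (r = 0.8). Not flagged.
- Anxiety t = 80, depression t = 55: total t = 50 + 10 × (3 × 1.5 + 0.5)/s = 72.9 or 71.0. Flagged. With k = 1 the total is 70.2 or 68.4, so the result depends on the assumptions.

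**Approximate counts.** The Sample size section plans 214 children and 40% attrition to week 6. Carrying that rate to 9 months (an assumption) leaves 214 × 0.6 ≈ 128.

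- Norm level: 128 × P(Z ≥ 2) = 128 × 0.0228 ≈ 3 children at or above 70 on depression. Missing 36–56% of them is 1 to 2 children.
- Shifted: 128 × P(Z ≥ 1) = 128 × 0.159 ≈ 20 children. Missing 20–30% is 4 to 6.

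**The case against.** The strongest reply concerns vocabulary. The article never defines a 25-item combined score. It uses total for the sum of each subscale: 0 to 30 for depression and 0 to 45 for anxiety. Table 1 lists the RCADS-25 only under depressive symptoms and under anxiety symptoms. A total t-score said to indicate depressive symptoms could therefore be the depression-subscale total, and the only fault would be a missing subscale name. That stands as a possible reading. It does not settle the matter, because the Monitoring sentence puts the total on the RCADS, and the article nowhere says that the subscale is meant.

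Other parts of the reply also stand. The percentages rest wholly on assumed correlation, spread and normality, and on the literal reading. In a norm-level sample they amount to one or two children. Raw totals alone (for example 30 of 75 against 45 of 75) cannot show who is flagged, because the trigger is a t-score and no norms are given. The depression efficacy analyses use the subscale and are unaffected. The K-SADS-COMP and the parent-reported diagnosis question also capture depression at 9 months, so depression reporting does not rest on this flag alone. The article ties no alert to either of them, however, so they do not replace the trigger.

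The statistical methods section is a weaker case. Without the word total, and after the article has tied depressive symptoms to the subscale, its t-score is at most an unnamed subscale.

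**Conclusion.** The point holds as an inconsistency between the Monitoring and Depressive symptoms sections that leaves a child-safety trigger open to two scorings. On the plain wording it scores a composite that is 60% anxiety. On the alternative reading it scores the depression subscale.

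The share of anxiety items comes from the article. The size of the disagreement does not. Under the literal reading, with bivariate normal subscales, equal per-item spread and r = 0.5 to 0.8, about 36–56% of children at or above t = 70 on depression would fall below 70 on the total at norm level, and 20–30% in a sample 1 SD above norm.

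A reader might infer more than the documents support. They do not establish that the trial actually scores the 25-item total. They do not say that a flagged child is told of severe depression: the pop-up advises seeking help, and the child is told that parents will hear they are having a hard time. Nor is any efficacy result on depression compromised. The point is worth correcting because the alert is live, the event count is reported, and the correction is small.

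**What to change.** Reconcile the Monitoring section with the Depressive symptoms section by naming the RCADS score that defines the event. An event labelled as depressive should be scored on the scale that the protocol uses for depressive symptoms. If the 25-item total is intended, relabel the event as combined anxiety and depression and report it as such. Check the Qualtrics trigger against whichever is chosen. For consistency, also name the score behind the exploratory comparison in the statistical methods section. The cut-off is for the sponsor, and none is proposed here.

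The cost is a wording amendment and at most one scoring line. Both subscales are already collected at 9 months, so no new data are needed. If the trigger is rescored, the number of flags may change.
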